### Sham-control condition

Participants assigned to the control condition will be introduced to three exercise modules (Modules A–C) that include seated exercises to improve core and arm strength and flexibility. All of the exercises are demonstrated to the participant by a physical therapist at the initial session. Participants will be provided a manual with thorough descriptions and visual aids of the seated exercises. Some of the exercises include use of a resistive (plastic air-filled) ball, which will also be provided to the participant. Participants will be instructed to start with Module A and continue for weeks 1–3, followed by Module B for weeks 4–6, and to finish with Module C for weeks 6–8. Participants will be told to follow the modules at their own pace. Each module includes approximately eight exercises that take 15–20 min to complete and participants will be told to work on the exercises three days per week. Participants will be provided a worksheet to record exercise days. Participants will be contacted by phone every 2–3 weeks during the 8-week intervention period to maintain engagement and encourage completion of the follow-up assessments.

The control is intended to account for a potential placebo effect and is considered a sham-control in that none of the exercises target lower extremity strength or flexibility, which is more likely to induce functional improvements and promote balance confidence during weight-bearing activities.

### Outcome measures

Outcomes will be collected before the start of the intervention (baseline) and again at 8 weeks (post-intervention), 16 weeks, and 24 weeks following group allocation.

#### Balance confidence (primary outcome measure)

Balance confidence will be measured through the Activities-specific Balance Confidence (ABC) scale. The scale asks participants to rate their level of confidence in completing 16 complex functional tasks without losing balance [21]. It has strong reliability (ICC = 0.91), internal consistency (Cronbach α = 0.95), and good construct validity in samples of older adults with fear of falling [22]. The ABC scale has also been validated to assess balance confidence in individuals with lower limb amputations [1].

#### Community integration

The following measures will be used to quantify community integration (secondary outcomes).

#### Activity monitoring

Participants will receive a SmartWatch3 Activity Monitor (SAM; Modus Health, WA, USA), which records stride count data for every minute of use, and a QStarz BT-Q1000XT (Qstarz International, Taipei) GPS travel recorder, which records a participant’s longitude, latitude, local time and date, and position every 10 s. The SAM and GPS will be worn for one week on the prosthetic pylon and then returned in a pre-paid envelope. Community integration will be assessed as the average number of steps/day, average number of steps/day taken outside the home, and total time spent outside the home per day. The individual who will link the GPS and activity monitor data to calculate steps/day as well as steps/day taken outside the home and total time spent outside the home per day will only be sent coded data so as to be blinded to the group inclusion.

#### Community Reintegration of Service members

Community Reintegration of Service members (CRIS) measures activity and participation with three subscales, extent of participation, perceived limitation, and participation satisfaction. The first two of the three scales are included in this study. The extent of participation scale evaluates the frequency of engaging in specific activities using seven-point scales (e.g., “In the past two weeks on average, how often did you engage in recreational activities, not including watching TV?”). The perceived limitation scale uses seven-point scales to evaluate self-perceived limitations in participation (e.g., “I avoided going to crowded places such as the mall of community gatherings”). The CRIS has been validated in a sample of injured veterans [23].

#### Short-Form Health Survey (SF36)

The SF36 consists of 36 questions that measure eight dimensions of health-related quality of life [24]. Three subscales, role limitation due to physical health problems, social functioning, and role limitations due to emotional problems, will be separately examined as secondary outcomes to assess community integration.

#### Frenchay Activity Index

The Frenchay Activity Index (FAI) is a 15-item behavioral scale that primarily measures social participation and daily activities (i.e., domestic/chores, work/leisure, and outdoor activities) [25]. Frequency of participation in activities over the last 3–6 months is rated on a four-point scale resulting in a single summary score, ranging from 0 (inactive) to 45 (highly active). The FAI is a valid and reliable measure among users of a LLP (ICC = 0.79) [26]. We will include the measure based on its association with the ABC scale in users with a LLP [4].

Additional secondary outcomes include quality of life and functional ability as described below.

#### Quality of life

The Well-being scale of the Prosthetic Evaluation Questionnaire (PEQ) will be used to assess quality of life (QoL) [27]. The PEQ is a survey that was developed to quantify function and prosthesis-related QoL for persons with lower limb amputation. The user marks a visual analog scale with two anchor points to respond to the following: “Over the past four weeks rate”…1) “How satisfied have you been with how things have worked out since your amputation” (anchors “extremely dissatisfied” and “extremely satisfied”)? and 2) “Your quality of life” (anchors “worst possible life” and “best possible life”). The simplified assessment allows participants to easily provide a summary of experiences by essentially considering QoL as unidimensional. This particular scale has good consistency (Cronbach α = 0.83) and reliability (ICC = 0.89) [28].

#### Functional abilities

The Berg Balance Scale (BBS) and L-test of walking will be used to measure functional abilities. Blinded assessors with prior training in administering these measures will assess performance.
*Berg Balance Scale*: This test requires participants to complete 14 tasks of increasing difficulty beginning with sit-to-stand and progressing to unipedal stance. It is a well-established outcome measure initially designed to assess balance in older adults [29] and has been validated for persons with lower limb amputation [8]. A blinded assessor who is unfamiliar with the study protocol will perform the assessments at baseline and follow-up.*L-test*: Participants rise from a chair without armrests, walk 3 m, turn right, walk 7 m, turn around and trace their path back to the start. The time to complete the task is recorded. The test has strong reliability (ICC = 0.98) and convergent validity (r = 0.93 with the Timed-up-and-Go test (TUG) [30]. The L-test is better than TUG at distinguishing changes in walking ability of fit, younger LLP users and it is as strong a predictor of social participation as is balance confidence [4]. The same blinded assessor who conducts the Berg Balance Scale will conduct the L-test.

### Data management and sharing

Data collection methods include the use of: 1) commercially available step count monitors and GPS trackers; 2) completion of pen-and-paper versions of validated clinical surveys; 3) scores on validated performance-based functional tests of balance. The methods for managing each type of data are nearly identical. Specifically, when a potential participant arrives at a study site to obtain informed consent, they will be assigned a study ID number that contains no identifiable information. Should that participant enroll in the study, then all data will be labeled and referenced only with the study ID number. For example, data from the monitors will be downloaded onto password-protected computers, assigned the appropriate ID, and then analyzed offline. All pen-and-paper data will only have ID numbers listed on them and no identifiable information (e.g., participant name) to ensure confidentiality. A single list linking names and codes will be kept on a password-protected computer locked in the PIs laboratory. All performance based data and pen-and-paper based outcomes data will be entered into an IRB-approved secure on-line data collection tool, Qualtrics, using the appropriate subject ID. Summative scores from Qualtrics will then be entered into electronic files on password-protected computers to further ensure confidentiality. De-identified data on Qualtrics can be shared among all research team members.

The study PI will periodically check the data values to ensure they are within range and will verify entries based on the original pen-and-paper versions, which will be stored in locked cabinets in the PI’s laboratory to further ensure confidentiality. All data will be stored for no less than 3 years following submission of the final financial report. A separate data monitoring committee is not required by the IRB or funding source for this study. However, the Human Research Protection Office (HRPO) of the US Army Medical Research and Development Command can perform an on-site audit at any time. To ensure confidentiality, information about an enrolled participant will only be shared with team members unless instructed otherwise by the HRPO.

While the final dataset will be stripped of identifiers prior to release for sharing, there remains the possibility of deductive disclosure of subjects given the somewhat small number of persons with transtibial amputation in the Chicago-land VHA system meeting the inclusion criteria of the study. Thus, we will make the final research data (both the raw and processed data) and any relevant documentation available to users only under a data-sharing agreement requiring investigators to commit to: 1) using the data only for research purposes and not for purposes of identifying participants; 2) properly securing the data; 3) destroying or returning the data after analyses are completed; 4) an agreement to share any new data sets resulting from the initial sharing agreement. The research and clinical community will be made aware of the data when the study results are presented at scientific meetings and in final publication form.

### Study administration

This trial will not include a coordinating center nor a Trial Steering Committee and there is no Stakeholder and Public Involvement Group involved. The study PI will undertake all administrative oversight, aside from that provided by the local IRB. He will have regular meetings with all investigators to discuss problems as they arise as well as progress of the study. The study PI will work with a study coordinator to identify potential recruits and consent will take place by any of the listed investigators on the study.

### Analysis plan

To test Hypothesis 1a we plan to use a 2 (group) × 4 (time point) mixed ANOVA to examine if there are significant differences in changes in ABC scores between the groups (i.e., an interaction effect), accounting for any missing data. In the event of a significant interaction, a post-hoc paired *t*-test will be used to compare ABC scale in the intervention group at 0 and 25 weeks and independent samples *t*-test to compare ABC scale between groups at 25 weeks.

To test Hypotheses 1b and 1c we will use a paired *t*-test to compare BBS scores and L-test times pre- and post-intervention. H1b and c do not compare time-related changes in performance between groups as they are only intended to assess the immediate effects of intervention.

The same analyses from Hypothesis 1a will be used to test all hypotheses in Aim 2. For Hypothesis 2a, a group × time interaction on self-reported community participation measures (CRIS, FAI, SF36 scales) and objective measures from the activity monitors will be tested. A false-discovery rate correction method will be used to minimize the likelihood of type I errors. For Hypothesis 2b, an interaction on the QoL score will be tested. In the event that H2a is not supported, alternative measures to assess integration will be considered.

To test Hypothesis 3 changes in ABC scores (0 weeks to 25 weeks) will be correlated with changes in self-reported and objective measures of community participation. A false-discovery rate correction method will be administered to minimize the likelihood of type I errors. In the unlikely event that Hypotheses 1a and 2a are not supported, this would not exclude the possibility of an association between subject-specific changes in confidence and participation. In such a case, a significant correlation would suggest that improving balance confidence can increase participation, but for optimum effectiveness of the intervention, one should only train individuals who are most likely to respond to the intervention (show large increase in ABC scores). As an initial step to identify commonality among “responders” we would employ a suite of supervised learning techniques (e.g., cluster and canonical correlation analysis) to explore multidimensional relationships among responses to individual items on the ABC, BBS, CRIS, and SF36.

To analyze intervention efficacy, the interviews will first be transcribed verbatim. After 15 interviews, all investigators will review the transcripts to generate an initial list of codes. After five additional interviews, they will again re-view transcripts to assess whether new codes emerged. If saturation is not reached after 20 interviews, another five participants will be interviewed and saturation will be reassessed. Once saturation is reached, lead investigators will review all transcripts to generate an initial list of codes using a content coding framework. The creation of the coding framework will begin by the identification of anything that participant’s mention related to the CBT strategies, the gaming exercises, activity restriction, or fear of falling/balance confidence. From this broad coding framework, responses will be sorted according to the themes. Brief descriptions of final codes will be created. A lead investigator will then meet with research assistants to discuss the coding structure. Research assistants will code three transcripts, meet to review discrepancies, and revise the codes, if necessary. Remaining transcripts will be coded individually; research assistants will then meet to resolve discrepancies. Final codes will be entered into NVivo, version 9 for analysis.

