**Fig. 1 Fig1:**
[figure not shown]
Flowchart of study participation

Participants in the intervention condition will complete eight weekly training sessions that include a virtual reality active gaming component (i.e., PT component), with CBT strategies that increase balance confidence by addressing subject-specific avoidance behaviors and maladaptive cognitions. Each session will last approximately 1.5 h. Participants in the control condition will complete a series of at-home upper-body seated exercises during this 8-week period after being taught by a physical therapist how to perform the exercises. The intention of the sham control is to blind participants to the study group. At the start of the study and at 8 (post-intervention), 16, and 24 weeks following group allocation, participants will complete survey-based outcome measures and activity monitoring. At baseline and post-intervention, participants will complete performance-based assessments of balance and of functional mobility. Outcomes measures are described below.

To minimize loss to dropout between baseline and final follow-up, research coordinators will routinely contact participants by telephone and email to maintain engagement in order to maximize participant adherence. Adherence will be quantified based on number of study visits attended and frequency of attendance. If a participant wishes to drop out of the study, they will be queried as to their reasons for doing so and every attempt will be made to address their concerns and to obtain the minimum amount of data necessary to address hypotheses related to the primary outcome (i.e., self-reported measures at 0 and 25 weeks).

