It is expected that 70 participants will be recruited in order to obtain a total of 60 eligible participants (30 intervention and 30 control participants), assuming a 15% drop-out rate. Using G*Power 3.1, a sensitivity analysis (with regard to Hypothesis 1a) was conducted, specifying a power of 0.80, an alpha of 0.05, and an average correlation of observations of 0.50. According to the analysis, with 30 participants in each group we will be able to detect a small to medium effect (f = 0.152) of intervention on ABC score over time with this design, which is consistent with the size of effect observed for older adults [10, 11]. We will have similar power for all hypotheses in Aim 2, which use the same analysis as Hypothesis 1a; we will have power to detect a medium effect size (d = 0.46) for Hypothesis 1b and a correlation of r ≥ 0.42 for Hypothesis 3.

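### The named primary test, a 2×4 mixed ANOVA, does not by itself use incomplete ABC records, although the retention plan treats first and last scores as enough for the primary-outcome hypotheses

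*Protocol article*

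**What the plan says.** - **Primary test.** For Hypothesis 1a the Analysis plan says "we plan to use a 2 (group) × 4 (time point) mixed ANOVA". The effect of interest is the difference between groups in change over time ("i.e., an interaction effect), accounting for any missing data"). No technique for the missing data is given.
- **Post-hoc tests.** Only if the interaction is significant, "a post-hoc paired *t*-test will be used to compare ABC scale in the intervention group at 0 and 25 weeks", together with a between-group t-test at the same final time.
- **Visits.** Outcomes are taken at baseline and "again at 8 weeks (post-intervention), 16 weeks, and 24 weeks following group allocation", which gives four time points. The final visit is 24 weeks here and 25 weeks in the Analysis plan. I treat them as one visit; the labels need reconciling.
- **Drop-outs.** Under Study design, staff will try to "obtain the minimum amount of data necessary to address hypotheses related to the primary outcome", spelled out as "i.e., self-reported measures at 0 and 25 weeks".
- **Numbers.** Study design randomises 60. The sample-size paragraph under Participants recruits 70 to end with 60, "assuming a 15% drop-out rate", and gives a detectable effect of f = 0.152 with 30 per group, power 0.80, alpha 0.05 and correlation 0.50.
- **Aim 2.** Every Aim 2 hypothesis takes the same analysis as Hypothesis 1a.

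**The concern.** Two statements do not fit together. One fixes a test on four scores per person. The other says that two of those scores are the least needed for the hypotheses that this test addresses. Someone with only the first and last scores has no 8- or 16-week value, and a classical mixed ANOVA, as ordinary software runs it, drops that person.

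Two things are at stake. One is power: records collected specifically to protect the primary outcome would not contribute to the primary test. The other is the randomised comparison. The intervention arm attends eight weekly sessions of about 1.5 hours, while the control arm exercises at home, so drop-out could plausibly differ by arm. If it also depends on how people respond, a complete-case comparison can be biased.

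Aim 2 inherits the problem. Its activity outcomes need a device worn for a week and posted back at each visit. Under complete-case ANOVA, one missed week would remove the person from that test.

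**Working it through.** **Step 1. Which ANOVA does the sample-size statement assume?**

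Inputs from Participants and Outcome measures: N = 60, k = 2 groups, m = 4 time points, correlation ρ = 0.50, alpha 0.05, power 0.80. Sphericity (ε = 1) is my assumption, as no correction is stated.

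Within-between interaction, noncentral F:
- λ = f² · N · m / (1 − ρ)
- df1 = (k − 1)(m − 1) = 3
- df2 = (N − k)(m − 1) = 58 × 3 = 174

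At f = 0.152, λ = 0.023104 × 60 × 4 / 0.5 = 11.09 and power = 0.798. Solving for power 0.80 gives f = 0.1524, so the stated 0.152 is reproduced. Alternatives do not match: three time points give 0.166, two give 0.184, and the between-subjects effect gives 0.291. The calculation is therefore for a classical mixed ANOVA with four scores from each of 60 people.

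**Step 2. Where can a record with only the first and last scores be used?**

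| Analysis | Scores needed | Usable? |
|---|---|---|
| Hypothesis 1a interaction (primary) | all four, under standard ANOVA | No |
| Post-hoc paired t-test, intervention arm | first and last | Yes, only after a significant interaction |
| Post-hoc between-group t-test | last | Yes, on the same condition |
| Hypothesis 3 correlation, intervention arm | first and last | Yes |

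The minimum data set fits the follow-up tests and Hypothesis 3, but not the test that decides Hypothesis 1a.

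**Step 3. Power if run on complete cases, f = 0.152**

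- *60 randomised, 15% incomplete:* 60 × 0.85 = 51. λ = 0.023104 × 51 × 4 / 0.5 = 9.43, df2 = 49 × 3 = 147, power = 0.721. The detectable f rises to 0.166.
- *60 left from 70 recruited:* 70 × 0.85 = 59.5. At N = 59, λ = 0.023104 × 59 × 4 / 0.5 = 10.91, df2 = 57 × 3 = 171, power = 0.790. At N = 60 it is 0.798.

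**Step 4. What would using the partial records recover?**

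Simulation, 1,500 runs. Assumed: 30 per arm, equal correlation 0.5, effect pattern 0, 1, 1, 1 scaled to f = 0.152, and 9 of 60 people, chosen at random, with first and last scores only. Power was 0.79 with full data, 0.72 with complete-case ANOVA and 0.77 with a within-subject analysis of all available scores.

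**Step 5. Could complete cases bias the estimate?**

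The protocol gives no drop-out by arm or by response, so this is illustration only. Simulation, 6,000 runs. Assumed: 30 per arm, correlation 0.5, true effect 0.60 SD at every follow-up.

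| Assumed drop-out | Complete cases | All first and last scores |
|---|---|---|
| 15%, unrelated to response | 0.595 | 0.597 |
| 20% CBPT and 10% control, CBPT drop-out related to poor week-8 change | 0.691 | 0.603 |

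A ceiling for the second row can be worked out. With correlation 0.5, change scores have SD 1, and week-8 change correlates 0.5 with final change. If exactly the worst fifth of the CBPT arm left, the shift would be 0.5 × 0.28 / 0.80 = 0.175 SD, where 0.28 is the normal density at the 20th percentile. The simulated shift of about 0.09 SD is half of that, so the assumed dependence is not slight. The right-hand column also assumes that every drop-out supplies a final score, which is the best case.

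**The case against.** A reader might infer that the plan restricts the primary test to people with all four scores and so excludes drop-outs. The document does not say that. No section prescribes listwise deletion or a complete-case set, and the sentence naming the ANOVA goes on to promise that missing data will be accounted for. A group-by-time model can be fitted to imputed data or to partial records in long format. A condensed article may also leave the technique to the full protocol or analysis plan. This stands: exclusion is a risk of the named method, not a stated rule, and an unnamed technique would not be a finding by itself.

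Nor does the retention text limit drop-outs to two scores. It sets a floor. Someone who leaves after week 16 and gives a final score has a complete record, and the number with only first and last scores is not stated. This also stands, so treating all 15% as incomplete is an upper figure at that drop-out rate.

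The loss to 51 may count drop-out twice, because the sample-size paragraph can be read as 60 already net of loss. Study design says 60 are randomised. The text supports both readings, so both are shown.

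What survives is the mismatch. The method named, and the method used for the sensitivity analysis, does not use the records that the retention plan calls sufficient.

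**Conclusion.** The concern holds as a conditional risk and an internal mismatch. Standard mixed ANOVA would leave out of the interaction test anyone with only first and last scores, and the promise to account for missing data names nothing that would bring them back.

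If the test is run on complete cases, power at f = 0.152 is about 0.72 instead of 0.80, provided that the 60 are those randomised and 15% are incomplete. It is about 0.79 to 0.80 if the 60 are what remains of 70, in which case the power cost is negligible. Both figures assume sphericity and correlation 0.50.

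Bias is possible if drop-out depends on response, and absent if it does not. The illustrated 0.69 against a true 0.60 SD rests on drop-out rates and a mechanism that are not in the documents. It should not be read as an estimate for this trial, nor as evidence that the randomised comparison is already broken.

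**What to change.** In the Analysis plan, replace the mixed ANOVA for Hypothesis 1a with a likelihood-based repeated-measures model that includes:

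- all randomised participants, analysed as allocated;
- every available ABC score, including first and last scores from drop-outs;
- visit as a categorical factor, group, and group by visit;
- the randomisation stratum (vascular or non-vascular cause).

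Keep the group-by-visit test as the primary test, so that the hypothesis is unchanged. Use the same model for Aim 2. Such a model is valid when missingness depends only on observed data. A sensitivity analysis that penalises drop-outs, or a single final-visit contrast, could be added, but this point does not require either.

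The cost is analysis wording and code. No extra data are needed. The one drawback is a model slightly less familiar to readers than ANOVA.

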## Methods/design

### Study design

Sixty people who use LLP with low balance confidence will be randomized to the CBPT intervention condition or control condition (Fig. 1). Participants will be assigned to one of two randomization plans based on etymology of amputation: vascular causes (e.g., diabetes, peripheral vascular disease) or non-vascular causes (e.g., trauma, osteomylistis). For each plan, a block randomization will be used with a block size of 4 to ensure balance among the exercise groups throughout the study. The randomization plan will be developed by a researcher uninvolved with the project using www.randomization.com and sealed envelopes will be used to conceal the randomization schedule until enrolled participants are assigned to a group. For scheduling purposes, to ensure that the necessary clinicians are on site at the time that group assignment is revealed to the participant (at visit occurring ~ 1 week following enrollment), envelopes will be opened after the participant leaves the university after completing the enrollment visit.

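### H1a is gated on a 3-df interaction and then read from an unadjusted last-visit t-test; the detectable f = 0.152 is right for the interaction but means roughly 0.6 to 0.8 SD between arms at the last visit

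*Protocol article*

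**What the plan says.** The Analysis plan section tests Hypothesis 1a with a 2 × 4 "mixed ANOVA to examine if there are significant differences in changes in ABC scores between the groups (i.e., an interaction effect"), that is, a group-by-time interaction in ABC. The next step is conditional: "In the event of a significant interaction, a post-hoc paired" t-test is run within the intervention arm (0 versus 25 weeks), together with an independent-samples t-test "to compare ABC scale between groups at 25 weeks". No baseline covariate is named for the between-group test. The same analysis is carried over to every Aim 2 hypothesis.

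The Participants section gives a sensitivity analysis for Hypothesis 1a with power 0.80, alpha 0.05 and correlation 0.50. It says that "with 30 participants in each group we will be able to detect a small to medium effect", namely f = 0.152, and adds "which is consistent with the size of effect observed for older adults". It gives no difference in ABC points or SD units and no time course.

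The Study design and Outcome measures sections schedule ABC at baseline and at 8, 16 and 24 weeks after allocation. Hypothesis 3, the drop-out paragraph and the Analysis plan speak of 25 weeks. Allocation is stratified: "Participants will be assigned to one of two randomization plans based on etymology of amputation" (vascular or non-vascular).

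**The concern.** Hypothesis 1a is directional: CBPT should improve balance confidence over time relative to control. A 3-df F test can be significant for any departure from parallel profiles, including a transient or reversed one. A statement that CBPT is better at the end of follow-up therefore has to come from the second step. That step has no stated power and discards the baseline ABC score, which every participant will have.

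The effect size is also easy to misread. In a repeated-measures interaction, f is the spread of the interaction cell effects. It is not half of a standardised mean difference, so a label that sounds modest on the f scale can stand for a large between-arm difference in ABC. A reader judging whether 60 participants are enough needs that difference.

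**Working it through.** **Inputs.** From Participants: 30 per arm (N = 60), alpha 0.05, correlation ρ = 0.50, f = 0.152. From the Analysis plan: 2 groups, m = 4 time points, hence df = 1 × 3 = 3 and 58 × 3 = 174. Assumed here: compound symmetry, equal SD at all visits, no missing data, and the time patterns listed below.

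**Step 1: reproduce the protocol's figure.** The noncentrality is λ = f²·N·m/(1 − ρ) = 0.152² × 60 × 4 / 0.5 = 11.09. With 3 and 174 df, power is 79.8%; the f that gives exactly 80% is 0.1524. The stated value is right.

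**Step 2: convert f to SD units.** With between-arm differences d₁…d₄ at the four visits and mean d̄, f² is the mean over visits of ((dₜ − d̄)/2)². For a step (0, d, d, d), d̄ = 0.75d, the mean squared deviation is 0.1875d², and f = 0.2165d. So d = 0.152/0.2165 = 0.70. For a linear rise (0, d/3, 2d/3, d), f = 0.1863d and d = 0.82.

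**Step 3: power at the last visit.** For the unadjusted t-test, the noncentrality is d·√(30/2). At d = 0.702 it is 0.702 × 3.873 = 2.72 on 58 df, giving 76%. The chance that the interaction and the t-test are both significant was simulated (40,000 trials per pattern).

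| Pattern at 0, 8, 16, 24 weeks | Last-visit difference for f = 0.152 | t-test alone | Interaction and t-test |
|---|---|---|---|
| 0, d, d, d | 0.70 SD | 76% | 62% |
| 0, 0, 0, d | 0.70 SD | 76% | 67% |
| 0, 0, d, d | 0.61 SD | 64% | 55% |
| 0, d/2, d, d | 0.73 SD | 80% | 66% |
| 0, d/3, 2d/3, d | 0.82 SD | 87% | 73% |

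The interaction has about 80% power in every row by construction. Under the step pattern its power is 48% at d = 0.5 and 19% at d = 0.3.

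**Step 4: adjust for baseline.** Adjustment multiplies the residual variance by 1 − ρ² = 0.75. The effective difference is 0.702/√0.75 = 0.81 and the noncentrality 0.81 × 3.873 = 3.14, which gives 87% by this approximation and about 86% by simulation. The difference detectable with 80% power falls from 0.736 SD unadjusted to 0.736 × √0.75 = 0.64 SD.

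**Step 5: effects that do not last.** With an effect at week 8 only (0.70 SD), the interaction is significant in about 80% of trials although the last-visit difference is zero. With a peak of 0.82 SD at week 8 fading to 0.27 SD, the interaction keeps 80% power, while the two-step sequence succeeds in about 13% of trials.

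**Step 6: fewer completers.** If 15% of 60 were lost, leaving 25 or 26 per arm, the two steps under the 0.70 SD step pattern would succeed in about 50 to 53% of trials. The protocol plans to recruit 70 to avoid this, so it is a sensitivity figure only.

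**The case against.** The strongest reply is that the protocol powers the test it names. The 80% refers to the interaction, the interaction is the stated test of Hypothesis 1a, and the figure is correct. A reader might infer that true power is 61 or 62% instead of 80%. The document does not support that: the lower figure is the joint chance of two significant results, and no power is claimed for the final-visit comparison.

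A reader might also infer that f = 0.152 simply is 0.70 SD. It is so only under particular time patterns, and the protocol states none. Nor can the comparison with older adults be called false. The small-to-medium label is attached to f, and the cited sources are not at hand. What can be said is that the scale of the comparison is not given.

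It is tempting, too, to read the protocol as already tying Hypothesis 1a to the last visit, because drop-outs will be asked for "the minimum amount of data necessary to address hypotheses related to the primary outcome (i.e., self-reported measures at 0 and 25 weeks"). That sentence sets the least data to retrieve. Hypothesis 3 needs the same two time points, and Hypothesis 1a says only that improvement occurs over time.

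Three further points stand. Baseline ABC is one of the four time points, so the interaction does use it; only the t-test ignores it. Adjustment for the stratum is often left to an analysis plan, so its absence is not a fault in itself. And where there is no last-visit effect, the second test limits a false last-visit claim, so the week-8-only example shows what the interaction cannot establish, not an error in the sequence as a whole.

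The objection does not remove the inefficiency of the between-group t-test, the gate in front of it, or the missing between-arm difference.

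**Conclusion.** The point holds as a mismatch between the test that is powered and the comparison that would support a last-visit conclusion. For lasting effects, f = 0.152 means 0.61 to 0.82 SD between arms at the last visit, so the small-to-medium label should not be read as a standardised mean difference. At a sustained 0.70 SD, the t-test alone has 76% power, the two planned steps together about 62% (55 to 73% across the lasting patterns examined), and a baseline-adjusted comparison about 86%. All of this rests on correlation 0.5, equal SDs, complete data with 30 per arm, and the assumed patterns.

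The 24 versus 25 weeks difference is minor but concerns the visit at which the arms are compared. Group assignment is revealed about a week after enrolment, which might explain it, but the protocol does not say so.

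**What to change.** Replace the unadjusted between-group t-test by a between-arm contrast at the last visit. Take it from a model with arm, visit, arm-by-visit, baseline ABC and the vascular/non-vascular stratum, and do not make it conditional on the interaction. Report the week 8 and week 16 contrasts and the interaction alongside, and use the same model for Aim 2.

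State the detectable effect also as a between-arm difference in ABC with its assumed time pattern: about 0.64 SD at the last visit for the adjusted contrast with 30 per arm and correlation 0.5. Put the comparison with older adults on that scale or leave it out. Use one label, 24 or 25 weeks, throughout, and define the time origin.

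The cost is analysis-plan wording and one restated figure; no extra data are needed. Whether the contrast becomes the primary test is a real choice, because Hypothesis 1a speaks of change over time. If it does, an effect that fades before the last visit loses power: in the fading example (0.27 SD at the end) the adjusted contrast would have roughly 20 to 25%, against 80% for the interaction. The choice should be made and recorded before outcome data are seen by arm.
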